### Baseline Site Assessments

3.4

The baseline efficiency of each hospital's colonoscopy surveillance process will be determined by calculating the staffing time burdens and costs for surveillance colonoscopy, as well as the appropriateness of each given surveillance interval, and time taken from colonoscopy until the patient receives communication regarding their next interval recommendation.

As per usual hospital practice, the next recommended colonoscopy surveillance interval will be provided to the patient and their family physician by the clinical team after colonoscopy. Compliance rates will be compared to the Australian guidelines for surveillance colonoscopy [6], and the time for each patient and their family physician to receive communication regarding the surveillance interval will be determined from medical records in a random selection of 10% of the total colonoscopies completed in 1 year (5% performed for surveillance and 5% for non‐surveillance indications) per hospital. Staffing time to provide the recommendations and communications will be prospectively determined for a minimum of 50 individuals undergoing surveillance colonoscopies at each hospital, with the costs calculated through consideration of time and salary rates. Clinical teams that are involved with the surveillance processes (proceduralists, nurses, administration and family physicians) will be interviewed to collect qualitative data on acceptability and limitations of current practices.

Surveys will be collected from a random selection of 100 patients per hospital before and after their surveillance colonoscopy, capturing patient demographics, assessing colonoscopy experience, quality of life and the quality of endoscopic services provided. Quality of life will be determined using the EQ‐5D‐5L validated measure [36].

Key performance indicators for the quality of endoscopic services (using recommendations provided in several consensus reports [6, 37, 38]; Table S1) will be calculated for a period of at least 6 months.

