**FIGURE 1 cam471456-fig-0001:**
[figure not shown]
A digital healthcare approach for automated colonoscopy surveillance recommendations, integrated with a nurse‐coordinated program.

Patients and family physicians will be informed of the prescribed surveillance interval and when the next surveillance colonoscopy is due, with the timing from colonoscopy until this communication recorded. Online surveys capturing the same patient‐reported measures collected at baseline will also be offered before and after surveillance colonoscopy, commencing at each hospital, 6 months after implementation of the intervention. In addition, interviews will be conducted with the clinical teams involved in the surveillance processes (proceduralists, nurses, administration and family physicians), to gauge end‐user acceptability. Measures of the key performance indicators for the quality of endoscopic services (Table S1) will be repeated at least 6 months after implementation of the intervention at each site.

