### Sample Size and Power

3.11

The stepped‐wedge cluster randomised trial includes five local health networks (cluster) with eight participating hospitals, contributing an average of 1417 colonoscopy episodes per 3‐month period (adjusted for 10% attrition) across seven sequential periods (one baseline and six rollout steps). Assuming an ICC of 0.01, a baseline guideline concordance of 60%, and an expected post‐implementation improvement to 75% (15% absolute increase), the design archives approximately 90% power at a two‐sided *α* = 0.05 under a binomial mixed‐effects model. Power was estimated via simulation (*n* = 1000 iterations per effect size), incorporating cluster and period fixed effects. A power curve (Figure S1) illustrates sensitivity to effect size assumptions, a stepped‐wedge design diagram (Figure S2) depicts the rollout sequence, and a summary of power estimates across effect sizes is presented in Table S3.

For the patient‐reported outcomes, assuming eight hospitals with paired before and after implementation (100 participants per hospital per period, total *N* = 1600), we estimate > 80% power (*α* = 0.05, two‐sided) to detect a small‐to‐moderate standardised mean difference (Cohen's *d* ≈ 0.25–0.30) in EQ‐5D‐5L scores, accounting for within‐cluster correlation (ICC ≤ 0.02) and within‐period correlation of repeated measures (*ρ* ≈ 0.5). This is appropriate for evaluating meaningful changes in patient‐reported measures at the hospital level.

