### Statistical Analyses

3.12

All sites will be allowed a three‐month post‐implementation period of transition before outcome measurement. Temporal confounding will be mitigated through the use of models (e.g., interrupted time series analysis) which adjust for secular trends. Given the stepped‐wedge cluster randomised design, analyses will explicitly include fixed effects for time period and intervention status, and random effects for site (cluster) to account for ICC. With only eight clusters, we will apply the Kenward–Roger correction to adjust standard errors and *p* values are not inflated due to small number of clusters. Data analysis will be conducted using Python (3.11) and R (version 4.4.1).

The percentage of surveillance recommendations that match with Australian guidelines will be calculated from audit data, and the prevalence of individuals lost to follow‐up, prevalence of those with acceptable colonoscopy quality, and incidence rates for advanced neoplasia and adverse events will be summarised using descriptive statistics. All measures will be directly compared to each site's own baseline measures in a paired manner using McNemar's tests for proportions, Wilcoxon and Kruskal–Wallis signed‐rank tests for continuous measures and mixed‐effects Poisson regression for incidence rates. Analyses will be conducted on an intention‐to‐treat basis. A prespecified generalised linear mixed model (GLMM) with a logit link will be used for the primary binary outcome (guideline concordance) including fixed effects for time period and intervention, random intercepts for clusters and adjustment for potential confounders (e.g., age, indication and baseline quality metrics). To address the small number of clusters (*K* = 5), we specify that inference will be based on cluster‐preserving parametric bootstrap for both the intervention coefficient and marginal contrasts. Multiple comparisons across secondary outcomes will be controlled using Holm–Bonferroni correction to limit type I error. Additional sensitivity analyses will include (i) cluster‐level summaries with Kenward–Roger correction, (ii) generalised estimating equations with small‐sample corrected SEs and (iii) permutation tests at the cluster level. If national guideline text changes during the trial, an indicator for the new guideline will be included, and analyses will be repeated using both old and new mapping.

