Where relevant, univariate followed by multivariable modelling will be undertaken by adding variables considered clinically important or statistically significant from the univariate model to adjust for confounding effects. Hospitals will be treated as random effects, and main effects will be the intervention group; that is, before and after implementation of the intervention. Missing data will be handled using multiple imputation under the missing‐at‐random assumption. For bowel preparation quality, missing values will be imputed as ‘adequate’ in the primary analysis, reflecting routine clinical documentation where poor preparation is explicitly noted, with sensitivity analyses applying conservative rules assumption imputing missing values as ‘poor’.

Multivariable generalised linear models and pairwise comparisons will be used to assess the association between patient‐reported measures (such as satisfaction with the colonoscopy experience) and acceptance of the digital healthcare approach. Thematic analysis will be conducted to establish clinical end‐user opinions on the surveillance program. Prespecified subgroup analyses will assess intervention effects across patient age, sex, socioeconomic status (by postcode linkage) and hospital location, with multiplicity controlled via Holm–Bonferroni correction. To ensure equitable healthcare delivery, analyses will include age groups ≥ 75 years, comorbidity burden (based on the Charlson Comorbidity Index categories), socioeconomic status and regional vs. metropolitan location.

Quality of life measures will be used to calculate the incremental costs before and after implementation of the intervention per quality‐adjusted life‐year gained (QALY) in a model‐based economic evaluation. Implementation costs will be obtained from administrative data. The economic evaluation will adopt a health‐system perspective with a 12‐month time horizon, 5% annual discounting and QALY derivation from EQ‐5D‐5L value sets. Probabilistic sensitivity analyses will assess parameter uncertainty, and reporting will align with CHEERS 2022 guidelines [43]. Patients will be recruited consecutively at each site, with reminders and follow‐up strategies implemented to maximise retention. Missing responses in surveys and quality‐of‐life instruments will be addressed using multiple imputation under the missing‐at‐random assumption, consistent with the approach for clinical outcomes.

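### The test named for EQ-5D-5L cannot use the pre-colonoscopy score that both phases collect: a cheap, low-priority gain in precision and case-mix control

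*Protocol article*

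**What the plan says.** **Collection.** For the control phase, section 3.4 (Baseline Site Assessments) states: "Surveys will be collected from a random selection of 100 patients per hospital before and after their surveillance colonoscopy", and "Quality of life will be determined using the EQ‐5D‐5L validated measure". For the intervention phase, section 3.8 (Implementation of the Digital Process) states: "Online surveys capturing the same patient‐reported measures collected at baseline will also be offered before and after surveillance colonoscopy". These later surveys start six months after implementation at each hospital.

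**Power.** Section 3.11 (Sample Size and Power) proceeds by "assuming eight hospitals with paired before and after implementation", with "100 participants per hospital per period" and a total of 1600. It claims more than 80% power for d of 0.25 to 0.30, allowing for an ICC of at most 0.02 and a "within‐period correlation of repeated measures" of about 0.5.

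**Analysis.** Section 3.12 (Statistical Analyses) states: "All measures will be directly compared to each site's own baseline measures in a paired manner using McNemar's tests for proportions". The same sentence goes on to give Wilcoxon and Kruskal–Wallis signed-rank tests for continuous measures. Baseline here means the site's pre-implementation phase, not the patient's score before the procedure. Section 3.12 also plans multivariable modelling where relevant, with variables chosen for clinical importance or univariate significance, and it derives QALYs from EQ-5D-5L value sets in a model-based evaluation.

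**Status.** Section 3.10 (Outcome Parameters) classes patient-reported measures as exploratory.

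**The concern.** Each surveyed patient supplies a score before the procedure, and so before the recommendation that follows from it. This is a patient-level baseline already paid for. The test named for continuous measures takes no covariate and leaves it out.

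Two things are at stake. The first is precision: a covariate correlated 0.5 with the outcome explains a quarter of the variance at the level where that correlation holds. The second is comparability. The total of 1600 counts the phases as separate patients, and sampling is described differently in different places: random selection in section 3.4, surveys offered online in section 3.8, consecutive recruitment in section 3.12. Patients in the two phases may therefore differ in health before the colonoscopy. Comparing a site with its own earlier values does not remove that difference.

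The point is separate from whether paired tests are valid on different patients. An unpaired or clustered comparison of post-colonoscopy scores would still leave the pre-score out.

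**Working it through.** **Inputs from section 3.11:** 8 hospitals; 100 patients per hospital per period (8 × 100 × 2 = 1600); ICC 0.02 (the upper limit given); rho 0.5; d = 0.25 with SD 1; two-sided alpha 0.05.

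**Assumptions needed because the article does not fix them:** rho is the correlation between a patient's pre- and post-colonoscopy scores; hospital-period effects are independent; normal reference distribution; no period effects.

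**1. Reproduce the plan's figure, without rho.**
- Variance of a hospital-period mean = ICC + (1 − ICC)/100 = 0.02 + 0.98/100 = 0.0298.
- SE of the phase contrast = √(2 × 0.0298/8) = 0.0863.
- z = 0.25/0.0863 = 2.90; power = Φ(2.90 − 1.96) = 82.5%. At d = 0.30 it is 93.5%.

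The stated figure of more than 80% is met.

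**2. Add the pre-score as covariate.** The variance factor is 1 − rho² = 1 − 0.25 = 0.75.

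| Where the factor applies | Variance of mean | SE | Power, d = 0.25 |
|---|---|---|---|
| Nowhere (unadjusted) | 0.0298 | 0.0863 | 82.5% |
| Patient-level part only | 0.02 + 0.98 × 0.75/100 = 0.02735 | 0.0827 | 85.6% |
| Whole variance | 0.75 × 0.0298 = 0.02235 | 0.0747 | 91.7% |

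The gain is about 3 points in the cautious case and about 9 if rho of 0.5 also holds between hospital-period means. For whole-variance adjustment, rho from 0.3 to 0.7 gives 85.9% to 98.2%.

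**3. Sensitivity to the reference distribution.** With a t reference on 14 df, the unadjusted and whole-variance figures are 76.8% and 87.5%; on 7 df they are 70.1% and 81.7%. In the other direction, if half of the hospital variance persists across phases and hospitals are compared with themselves, unadjusted power is 94.4% (normal). The article does not say which applies.

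**4. Case mix (illustrative).** With equal SDs, the slope of post-score on pre-score is rho. A pre-score difference of 0.10 SD between phases then shifts the unadjusted post-score contrast by 0.5 × 0.10 = 0.05 SD, which is 0.05/0.25 = one fifth of the smaller target effect. A change score moves it the other way: 0.05 − 0.10 = −0.05 SD. Adjustment removes the shift. In a simulation with no true effect (4000 runs, t with 14 df, rho 0.5 at both levels), the mean estimate was 0.052 unadjusted and 0.001 adjusted, with rejection rates of 8.8% and 5.5%.

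**5. QALYs (assumed form).** If QALYs were a two-point area under the curve over 12 months, a baseline utility gap of 0.02 would add 0.5 × (0.02 + 0.5 × 0.02) = 0.015 QALY. The article does not state this calculation, so the figure shows scale only.

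**The case against.** **The plan may adjust anyway.** Section 3.12 promises multivariable modelling for confounding where relevant, with hospitals as random effects, and fixed effects for period and intervention. Nothing excludes the pre-score, and a covariate list for an exploratory outcome may sit in the analysis plan. This stands in part: a reader might infer that the plan rules adjustment out, and it does not. But the clause names no variable, selects partly on univariate significance, and sits beside a named test that takes no covariate.

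**QALYs.** A reader might infer that the QALY calculation wrongly omits baseline utility. The article is silent rather than contrary. It describes a model-based evaluation and states no QALY regression. This objection stands.

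**Power.** A reader might infer that the comparison is underpowered, or that rho is shown to be unused because 82.5% is reached without it. Neither follows. The claim is an inequality that several formulas satisfy, and the wording does not show how rho entered.

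**Period effects.** The figures above omit the period effects that section 3.12 prescribes. Including them lowers power, by an amount that depends on survey timing and rollout order, which the article does not give. If each network is surveyed just before its own rollout and again one step later, one calculation gives 73% unadjusted and 85% adjusted; two steps later, 60% and 72%. If all control surveys fell in one common period before rollout, with no control surveys later, phase and period could not be separated at all. This stands as a limit on the absolute figures. It affects the unadjusted analysis equally and is no argument against the covariate.

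**Conclusion.** The point holds in a limited form. The pre-colonoscopy EQ-5D-5L is collected in both phases and a repeated-measures correlation is counted in section 3.11, but the test named in section 3.12 cannot use the score and no passage commits to adjusting for it. The cost is forgone precision and unremoved case mix, not a failed power claim.

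The gain is about 3 points of power (82.5% to 85.6%) if only patient-level variance shrinks, and up to about 9 (to 91.7%) under the stronger assumption on hospital-period variance. Both figures rest on a two-phase contrast without period effects and on reading rho as the within-patient pre/post correlation. The 0.05 SD shift is an illustration, since nothing in the article says how far the phases will differ. Adjustment removes only the case mix that the pre-score captures.

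EQ-5D-5L has its own power statement and feeds cost-effectiveness, a listed secondary outcome. Patient-reported measures are nevertheless exploratory, so this is a low-priority improvement.

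**What to change.** In section 3.12, replace the signed-rank test for EQ-5D-5L with a linear mixed model of the post-colonoscopy score that has the patient's pre-colonoscopy score as a covariate. Keep the period and intervention fixed effects, the random effects and the small-cluster correction already stated there. No extra nesting of hospitals within networks is needed; with five networks, two of them with a single hospital, it would be poorly estimated.

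In section 3.11, say what rho refers to and how it enters the calculation. Where patient-level EQ-5D-5L data feed the QALY estimate, state that it is adjusted for pre-colonoscopy utility.

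The change needs wording only and no new data. There are two downsides. Patients with one of the two surveys will rely on the multiple imputation already planned. The adjustment also assumes that SCOPES has not already affected the pre-score, for example through recall or scheduling; that assumption should be stated.

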### Data Governance and Safety Monitoring

3.9

All study data will be stored on secure institutional servers compliant with role‐based access control, multifactor authentication and encrypted data transmission between participating sites. Automated audit logs will record all data modifications and algorithm interactions. To mitigate automation bias, nurse coordinators will review and confirm all algorithm‐generated recommendations using a structured checklist before acceptance into the patient record. A data and safety monitoring plan will oversee potential harms such as delayed colonoscopies or missed advanced neoplasia.

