### Outcome Parameters

3.10

All study outcomes will be compared between baseline and post‐intervention measures. The primary outcome is the proportion of automated interval recommendations for surveillance colonoscopy that match those derived from a prespecified ruleset directly based on the Australian guidelines. This ruleset serves as the gold standard for interval assignment and is explicitly programmed from the most recent national surveillance criteria. Algorithm outputs will be independently compared against this reference ruleset, with nurse recommendations serving as a secondary comparator. Validation will be conducted blinded to algorithm outputs to avoid bias, and any discrepancies between algorithm, ruleset and clinical recommendations will be adjudicated by an independent gastroenterologist panel.

Secondary outcomes include:
The timing of the scheduled colonoscopy in relation to the recommended timeframe, with ‘on‐time’ colonoscopy defined as occurring within ±6 months of the due date specified by guideline recommendations.The time taken to review the colonoscopy outcomes and communicate the prescribed surveillance interval with the patient and family physician.The prevalence of individuals lost to follow‐up.The prevalence of patients with acceptable bowel preparation quality, complete intubation and adequate withdrawal time.The incidence rate for advanced neoplasia (with hierarchical classification prioritising invasive CRC > stage 0 CRC > advanced adenoma), including CRC, adenomatous polyps or sessile serrated lesions ≥10 mm in size, with villous change, or with high‐grade dysplasia, sessile serrated lesions with any dysplasia and any traditional serrated adenoma.The incidence rate for adverse events (e.g., bleeding, perforation, hospitalisation and death).Acceptability of the intervention to patients and clinical teams.Cost‐effectiveness of the intervention.Among the secondary outcomes, those relating to colonoscopy quality metrics and timeliness are confirmatory and prespecified, whereas patient‐reported measures and thematic feedback analyses are exploratory.

Trial findings will be reported according to the CONSORT‐AI extension guidelines [42].

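### The Holm–Bonferroni correction, as worded, includes the adverse event comparison and so makes a true rise in adverse events less likely to be declared

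*Protocol article*

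**What the plan says.** Section 3.12 (Statistical Analyses) fixes the multiplicity rule for the secondary outcomes in one sentence: "Multiple comparisons across secondary outcomes will be controlled using Holm–Bonferroni correction to limit type I error". It names no exception and gives no list or count of the tests in the family.

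Section 3.10 (Outcome Parameters) includes this among the eight listed secondary outcomes: "The incidence rate for adverse events (e.g., bleeding, perforation, hospitalisation and death". Two others bear on the point: "The incidence rate for advanced neoplasia" and "The prevalence of individuals lost to follow". The same section calls the quality and timeliness outcomes confirmatory and the patient-reported and thematic work exploratory. Adverse events are placed in neither tier.

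Section 3.12 says first that "incidence rates for advanced neoplasia and adverse events will be summarised using descriptive statistics". The next sentence has every measure compared with the site's own baseline and names "mixed‐effects Poisson regression for incidence rates" as the method for rates. Adverse events are therefore both described and tested.

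Section 3.9 (Data Governance and Safety Monitoring) adds: "A data and safety monitoring plan will oversee potential harms such as delayed colonoscopies or missed advanced neoplasia". It gives no test or threshold for harm.

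**The concern.** A multiplicity correction lowers the chance of at least one false positive across a set of claims. That is the right protection when each positive would be reported as a benefit. For adverse events the costlier error is the opposite one, a real increase that is not declared. Holm adds to that error, because the adverse event p-value must clear a threshold that may be as low as 0.05 divided by the number of tests.

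In practice, a rise in bleeding, perforation, hospitalisation or death with an unadjusted p-value of, say, 0.02 could be written up as not significant after correction. The programme changes how recall is organised across five hospital networks and is meant to be considered for wider use, so the safety comparison should not be blunted by how many unrelated outcomes share its family.

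**Working it through.** The article gives no power, event rate or adjusted alpha for adverse events, so there is no figure of its own to reproduce. The 90% power in section 3.11 concerns the primary outcome and is not used here.

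**Step 1. Is the adverse event test in the family?** Three statements settle the plain reading: Holm covers the secondary outcomes (3.12), adverse events are a secondary outcome (3.10), and incidence rates are formally compared (3.12). The tiering in 3.10 does not take adverse events out, because 3.12 does not limit Holm to the confirmatory tier.

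**Step 2. Inputs for the illustration**
- Family alpha: 0.05 two-sided. Section 3.11 states this for the primary and patient-reported outcomes. It is assumed here for the secondary family.
- Family size m: not stated. There are 8 listed outcomes, or 6 without acceptability and cost-effectiveness. There are 13 if the three quality items and the four adverse event examples are counted singly (8 + 2 + 3).
- Power of the adverse event test at 0.05: not stated. Values of 80% and 90% are assumed.

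**Step 3. Strictest Holm step**

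Threshold = 0.05/m. Power there = Φ(z(0.975) + z(power at 0.05) − z(1 − 0.05/(2m))).

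For 80% the first two terms sum to 1.960 + 0.842 = 2.802. For 90% they sum to 1.960 + 1.282 = 3.242.

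| m | Threshold | Critical z | From 80% | From 90% |
|---|---|---|---|---|
| 6 | 0.0083 | 2.638 | Φ(0.164) = 56.5% | Φ(0.604) = 72.7% |
| 8 | 0.00625 | 2.734 | Φ(0.068) = 52.7% | Φ(0.508) = 69.4% |
| 13 | 0.0038 | 2.891 | Φ(−0.089) = 46.5% | Φ(0.351) = 63.7% |

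**Step 4. Full step-down procedure**

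Holm relaxes the threshold each time an outcome is rejected. A simulation with m = 8, independent tests, 200,000 runs and 80% unadjusted power for the harm test gives:

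| Other outcomes with a strong effect | Power for the harm |
|---|---|
| 0 | 52.8% |
| 2 | 56.6% |
| 4 | 62.1% |
| 7 | 79.9% |

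With m = 6 and no other effects the figure is 56.6%. The loss disappears only when all the other outcomes are rejected.

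**Step 5. Dependence on event rates**

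This uses hypothetical rates, equal numbers per phase and no allowance for clustering. Power = Φ(ln RR / √(1/E0 + 1/E1) − critical z), where E0 and E1 are the expected events in each phase. Section 3.11 does not make clear whether 1417 episodes per period is a total or per network, so both readings are shown: 1417 × 7/2 ≈ 4,960 and 1417 × 5 × 7/2 ≈ 24,798 colonoscopies per phase.

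| Per phase | Baseline rate | Rate ratio | Power at 0.05 | Power at 0.05/8 |
|---|---|---|---|---|
| 4,960 | 0.5% | 2.0 | 80.5% | 53.3% |
| 24,798 | 0.2% | 1.5 | 59.9% | 30.1% |
| 24,798 | 0.5% | 1.5 | 93.8% | 77.7% |
| 24,798 | 0.5% | 2.0 | 100.0% | 100.0% |

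The correction costs most at moderate power and nothing when the harm is large and events are plentiful.

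**The case against.** The best reply has four parts.

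- **Family membership is inferred.** One general sentence in a condensed article does not list the tests, and an analysis plan could define the family more narrowly. This stands in part. But the article does fix a rule without exception, so a plan that exempted adverse events would depart from the published wording.
- **The figures depend on assumptions.** Family size and starting power are not stated. Cost-effectiveness is evaluated as incremental cost per QALY, and acceptability largely through interviews and exploratory measures, so six is arguably a more natural count than eight. The strictest step applies only if nothing else is rejected first, and the intervention acts directly on communication time and scheduling. All of this stands, so the result is a range.
- **Harms are also handled elsewhere.** Rates are summarised descriptively, and section 3.9 provides a monitoring plan and nurse confirmation of each recommendation. Nothing says that a non-significant adjusted result will be read as safety. This softens the consequence but does not remove the correction from the final comparison.
- **The harm argument does not reach every outcome that sounds like safety.** A reader might infer that loss to follow-up and advanced neoplasia should be exempted on the same grounds. The article does not support that. The Introduction presents loss to follow-up as a weakness of current referral, so a reduction would be claimed as benefit and needs the correction. Advanced neoplasia has no stated harm direction: section 3.3 treats lesion detection as part of colonoscopy standards, so a higher rate may mean better detection. The harm in section 3.9 is missed neoplasia, which is not the incidence rate in section 3.10.

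**Conclusion.** The point holds for adverse events. As worded, section 3.12 puts their formal comparison inside the Holm family, and that lowers the chance of declaring a true increase. If the test has 80% power at 0.05, the strictest step leaves about 57% with six outcomes or 53% with eight. Power recovers to about 62% with four other strong effects among eight, and recovers fully only if every other outcome is rejected. These figures assume a family alpha of 0.05, independent tests in the simulation and an illustrative starting power.

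A reader might go further and conclude that every harm must clear a threshold of 0.05/8, or that the trial will give false reassurance on safety. Neither follows: the threshold lies between 0.05/m and 0.05 depending on the other results, and the article does not say how a non-significant adverse event result will be interpreted. This is a cheap improvement to the wording, not an error that threatens the primary analysis.

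**What to change.** In section 3.12, add that adverse events are outside the Holm–Bonferroni family, are reported with effect estimates and unadjusted 95% confidence intervals, and that no claim of safety will be drawn from a non-significant p-value.

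Keep Holm for the confirmatory timeliness and quality outcomes and for any other secondary outcome on which benefit would be claimed, including a reduction in loss to follow-up. Advanced neoplasia need not be exempted as a harm outcome.

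The cost is one sentence, with no new data and no change to the primary analysis. The downside is more chance signals: one adverse event test at 0.05 gives a 5% false alarm rate, and four components tested separately would give 1 − 0.95⁴ = 18.5% if independent. Such signals are interpreted clinically. A small gain is that the remaining family shrinks by one, for example from a first step of 0.05/8 = 0.00625 to 0.05/7 = 0.0071.

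### Univariate significance alone can bring a variable into models of the intervention effect, with no timing limit and no exemption for the primary model

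*Protocol article*

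**What the plan says.** All the relevant text on modelling is in Section 3.12 (Statistical Analyses) of the protocol article.

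- **Primary model.** "A prespecified generalised linear mixed model (GLMM) with a logit link will be used for the primary binary outcome". It has fixed effects for period and intervention, random intercepts for clusters, and "adjustment for potential confounders (e.g., age, indication and baseline quality metrics". The covariates are given as examples, so the list is open.
- **Selection rule.** Further on, under a qualifier limiting it to cases where it is relevant, univariate models are followed by multivariable ones that add "variables considered clinically important or statistically significant from the univariate model to adjust for confounding effects". The stated purpose is control of confounding. The two criteria are joined by *or*.
- **What those models estimate.** The next sentence says that hospitals are random effects and that "main effects will be the intervention group", meaning before versus after implementation.
- **Data source for concordance.** "The percentage of surveillance recommendations that match with Australian guidelines will be calculated from audit data". Section 3.4 (Baseline Site Assessments) describes the baseline audit as a "random selection of 10% of the total colonoscopies completed in 1 year" per hospital.
- **Quality measures as outcomes.** Section 3.10 (Outcome Parameters) lists as a secondary outcome "The prevalence of patients with acceptable bowel preparation quality, complete intubation and adequate withdrawal time". It also calls the colonoscopy quality and timeliness outcomes confirmatory and prespecified.

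**The concern.** A confounder is related to both exposure and outcome. Exposure here is fixed by site and calendar time. A univariate p-value against the outcome says nothing about the exposure side, and it depends heavily on how many records are analysed.

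The rule also sets no limit on when a candidate variable is measured. Table 2 of the protocol article collects bowel preparation, intubation distance and withdrawal time for procedures throughout, and Section 3.6 feeds procedure quality into the interval algorithm. An association with concordance is therefore plausible. The plan itself treats these measures as things that may differ after implementation. If their post-go-live values enter as covariates, the adjusted estimate is no longer the total effect of the programme.

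Two things are at stake. The adjusted intervention effect could depend on a selection made after outcomes are seen, with a different covariate set for each outcome. Part of the effect could also be adjusted away.

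**Working it through.** **1. What the text allows.** The plan states no figure for covariate selection, so there is none to reproduce. Set side by side, the primary model is called prespecified but has an open covariate list. The selection rule makes univariate significance sufficient, names no candidates and no time window, and applies to models with the intervention as main effect. Nothing says whether it reaches the primary model.

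**2. How weak a variable can be and still enter.** Inputs from Section 3.11 (Sample Size and Power) are five networks, seven periods, 1417 episodes per 3-month period, and concordance of 60% and 75% (midpoint 0.675). The text does not say whether 1417 is per network or in total:

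- per network: 5 × 7 × 1417 = 49,595 episodes;
- in total: 7 × 1417 = 9,919 episodes.

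If only a 10% audit sample carried the concordance outcome throughout (an assumption, since 10% is stated for the baseline audit), these become about 4,960 and 992.

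For a 50:50 binary covariate, ignoring clustering:

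- SE(log OR) = √[4 / (N × 0.675 × 0.325)];
- OR with 80% power to reach p < 0.05 = exp(2.8 × SE);
- smallest significant difference in concordance = 1.96 × √[0.675 × 0.325 × 4 / N].

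| N analysed | SE(log OR) | OR with 80% power | Smallest significant difference |
|---|---|---|---|
| 49,595 | 0.0192 | 1.06 | 0.8 points |
| 9,919 | 0.0429 | 1.13 | 1.8 points |
| 4,960 | 0.0606 | 1.19 | 2.6 points |
| 992 | 0.1356 | 1.46 | 5.8 points |

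The planned effect is 15 points. Trivial associations pass if all episodes are analysed. At about 1,000 audited records that argument is weak.

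**3. Pure noise.** With k independent null candidates tested at 0.05, the chance that at least one enters is 1 − 0.95^k: 40% for k = 10 and 64% for k = 20. The values of k are assumptions.

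**4. Adjusting for a consequence of the intervention.** The illustration used 200 simulated trials with 5 clusters, 7 periods and 283 episodes per cluster-period (1417 / 5), ICC 0.01, and a target intervention log OR of ln[(0.75/0.25) / (0.60/0.40)] = ln 2 = 0.693. Two inputs are assumed: the intervention moves a binary quality variable from 60% to 85%, and that variable has OR 2 with the outcome.

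- The variable passed univariate screening in 100% of runs.
- Mean intervention log OR without it: 0.687 (OR 1.99).
- Mean intervention log OR with it: 0.519 (OR 1.68).

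The loss is close to ln(OR of variable) × shift in prevalence = 0.693 × 0.25 = 0.173. This gives an approximate range. With no shift nothing is lost. With half the assumed shift, the loss is 0.693 × 0.125 = 0.087, and the OR is exp(0.693 − 0.087) = 1.83. The full shift gives about 1.7.

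**The case against.** The strongest defence has five parts.

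- **Scope.** The primary outcome has its own model, called prespecified, and the selection rule carries a qualifier, so it can be read as covering other models. A reader might infer that the two statements flatly contradict each other. They do not; the scope is unclear. What stands is that nothing exempts the primary model. Even on the narrow reading, the rule still covers intervention-effect models for other outcomes, some of which Section 3.10 calls confirmatory.
- **Detail left to an analysis plan.** A closed covariate list is commonly left there, and the open list alone would not be a finding. The selection rule, however, is written into the protocol article.
- **Dropped confounders.** A reader might infer that real confounders would often be screened out, especially with 100 patients per hospital and period. The documents do not support this. Variables judged clinically important enter whatever their p-value. The models pool hospitals, and the site-versus-own-baseline tests (McNemar, Wilcoxon) use no covariates. At the pooled N = 1600 for patient-reported outcomes, a correlation of 0.15 gives z = atanh(0.15) × √1597 ≈ 6.0 before clustering, so it would almost never be missed.
- **Weak covariates do little harm.** This is right. Type I error stayed near 5% in a simple simulation of screening, so the sample-size table shows how permissive the rule is and does not measure bias.
- **Post-go-live adjustment is not stated.** This is also right. The only quality covariates named are baseline ones. A reader might infer that the plan intends to adjust for post-implementation measures; it only fails to rule this out.

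**Conclusion.** The point holds as a minor one. As written, the rule makes univariate significance a sufficient reason to add a variable to models of the intervention effect. It has no timing restriction and no exemption for a primary model described as prespecified. It cannot identify confounders, and it would admit variables that are themselves secondary outcomes.

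No single size can be given. The attenuation from OR about 2.0 to 1.7 rests on an assumed shift of 25 points and an assumed OR of 2. It is zero if the intervention does not move the variable. The entry thresholds depend on which records are analysed: OR about 1.06 to 1.13 with all episodes, about 1.19 to 1.46 with a 10% audit sample. The broader claim that almost any variable would pass is therefore not established, because concordance is to come from audit data. No inflation of test size is claimed.

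**What to change.** In Section 3.12:

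- Remove univariate screening from every model that estimates the intervention effect, and say that this includes the primary mixed model.
- Replace the example list with a fixed set, used alongside the period effects: age, sex, indication, Charlson category, socioeconomic status, and the baseline quality metrics already named, defined as pre-implementation values. All of these are already collected or planned (Table 2, Sections 3.4, 3.6 and 3.12).
- State that variables measured after go-live which the intervention can change, including bowel preparation, intubation and withdrawal time, are not covariates in these models.
- Keep univariate screening, if wanted, for exploratory association models only, such as those relating patient-reported measures to acceptance of the digital approach.

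The cost is wording. No stated figure changes. The fixed set may carry one or two weak covariates, at negligible cost in precision.
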